### Duration of follow-up

On the same day as randomization, which is counted as day 0, 10 mL peripheral blood samples will be collected. For the ddPCR group, blood samples will be sent for ddPCR tests and a synchronous blood sample will be collected for blood culture. Among them, the patients with positive ddPCR results for the first time on day 0 will have blood collected for monitoring on day 3, day 7, and day 7n(n > 1, that is, every seven days, until there is a clinical outcome). The patients with negative results for the first time on day 0 will have blood collected every seven days (on day7n, n ≥ 1). And if necessary, physicians can apply for an additional test for them at any time after day 3. For the control group, blood samples will be collected on day 0, and stored in the laboratories of participating institutions without applying the ddPCR test. The blood samples can be used for other microbiological tests such as mNGS, and any other microbial examinations are accessible to both the experiment group and the control group.

Apart from tests to identify pathogens, follow-up examinations also include laboratory examinations and physical examination results to calculate the severity of disease scores including SOFA and disseminated intravascular coagulation (DIC) scores. These are results of routine blood tests, serum C-reactive protein (CRP), procalcitonin (PCT), erythrocyte sedimentation rate (ESR), D-Dimer, arterial blood gas tests, blood culture, body temperature, respiratory rate, blood pressure, heart rate, state of consciousness and so on. Demographic information will be collected when patients are enrolled, and prognosis information when there is a patient outcome such as discharge or in-hospital death. Patients will also be phoned on day 90 for their conditions (survive or death) and an EQ-5D quality of life score.

### Sample size calculation

The predicted sample size is calculated to achieve the primary outcome, which is evaluating the diagnostic test accuracy of the ddPCR method (our index test) compared with the reference test.

According to previous published studies evaluating diagnostic accuracy of ddPCR in patients with suspected sepsis, expected test sensitivity (SN) and specificity compared with blood culture are 85% and 75%, respectively according to our pre-test and the previous studies [11, 14]. And the estimated disease prevalence (P), which is the blood culture positive rate in this case, is around 3% to 15% [5, 21, 22]. Therefore, based on the sample size calculation statistical methodology incorporating in the prevalence of disease [23, 24], with a significance ($$\alpha$$) level of 0.05, a 95%CI width of 10% and a prevalence of 3%, the sample size for the experimental group is:$$\mathrm{N}1=\frac{TN+FN}{P}= {Z}\alpha^2/2\frac{SN(1-SN)}{{W}^{2}*P}=1632.$$

Since patients will be allocated into two groups with a ratio of 3:1, the total sample size of the two groups combined is 1632/3*4 = 2176. Assuming a 5% drop-out rate in follow-up, the sample size is calculated to be 2292 patients.

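### The stated 95% CI width of 10% for sensitivity is really a half-width: at the planning prevalence, 1632 patients give an interval about 20 points wide

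*Protocol article*

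**What the plan says.** The Sample size calculation section of the protocol article bases the trial's size on the accuracy of ddPCR against blood culture, which is the primary outcome. Its inputs are:

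- Accuracy: "expected test sensitivity (SN) and specificity compared with blood culture are 85% and 75%, respectively". Only the sensitivity enters the formula.
- Prevalence: "estimated disease prevalence (P), which is the blood culture positive rate in this case, is around 3% to 15" per cent. The calculation uses the lower end.
- Precision: "a 95%CI width of 10% and a prevalence of 3%, the sample size for the experimental group is", followed by a formula whose result is 1632. The formula is z² × SN(1−SN) / (W² × P), with z taken at α/2. Its left-hand side is written as (TN+FN)/P.
- Allocation: "the total sample size of the two groups combined is 1632/3*4 = 2176". A 5% drop-out allowance then brings the total to 2292.

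Only the ddPCR arm contributes to the sensitivity estimate. Under Duration of follow-up, control-arm day-0 samples are "stored in the laboratories of participating institutions without applying the ddPCR test".

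**The concern.** The width of a confidence interval is ordinarily the distance between its two limits. In the formula printed, W is the distance from the estimate to one limit, because it is obtained by solving W = z × √(SN(1−SN)/n) for n. Entering the stated 10% as W therefore delivers plus or minus 10 points, not an interval 10 points wide. Nothing in the article says that width means half-width.

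This is the only precision target given for the primary outcome, and it applies to sensitivity. A reader would expect an interval of roughly 80% to 90% if the assay performs as assumed. The design gives roughly 75% to 95% at the planning prevalence, which cannot separate a moderate assay from an excellent one with the precision claimed.

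The numerator adds to the confusion. The article defines P as the culture-positive rate, so the count divided by P must be the culture-positives. Under Diagnostic methods these are TP plus FN, where FN also takes in non-overlapping detections. TN+FN is a different group.

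**Working it through.** **Inputs**, all from the Sample size calculation section: SN = 0.85, P = 0.03, α = 0.05 two-sided (z = 1.96), stated width 10%, allocation 3:1, drop-out 5%.

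**Step 1: reproduce 1632.** Number of culture-positives = z² × SN(1−SN) / W², divided by P for the arm size.

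| z | W entered | Culture-positives | ddPCR arm |
|---|---|---|---|
| 1.96 | 0.10 | 3.8416 × 0.1275 / 0.01 = 48.98 | 48.98 / 0.03 = 1632.7 |
| 1.96 | 0.05 | 3.8416 × 0.1275 / 0.0025 = 195.9 | 195.9 / 0.03 = 6530.7 |
| 1.645 | 0.10 | 34.5 | 1150 |
| 1.645 | 0.05 | 138.0 | 4599 |

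The one-sided rows are included because the Statistical methods section exempts the primary outcome from two-sided testing. Only two-sided z with W = 0.10 gives the plan's figure. The later steps also hold: 1632 × 4/3 = 2176, and 2176 / 0.95 = 2290.5, against the stated 2292.

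**Step 2: the interval that 1632 patients give at 3%.** 1632 × 0.03 = 49 culture-positives. Half-width = 1.96 × √(0.1275/49) = 0.100, so the interval is 75% to 95% and its width is 20 points. Other interval methods agree. With 42 of 49 detected, the Wilson interval is 73.3% to 92.9% (19.6 points) and the Clopper-Pearson interval is 72.8% to 94.1% (21.3 points).

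**Step 3: does the drop-out allowance close the gap?** Three quarters of 2292 is 1719. With no losses at all, 1719 × 0.03 = 51.6 culture-positives and the total width is 19.5 points.

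**Step 4: width across the plan's prevalence range,** with 1632 patients and SN = 0.85.

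| Culture positivity | Culture-positives | Total 95% CI width (points) |
|---|---|---|
| 3% | 49 | 20.0 |
| 5% | 82 | 15.5 |
| 10% | 163 | 11.0 |
| 15% | 245 | 8.9 |

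A 10-point total width needs 196 culture-positives, and 196/1632 = 12.0% positivity.

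**Step 5: size needed for a 10-point total width at 3%.** 6531 in the ddPCR arm, 6531 × 4/3 = 8708 in total, and 8708 / 0.95 ≈ 9167 with drop-out.

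**Step 6: the numerator.** At the plan's own inputs, TN+FN would be about 1632 × (0.97 × 0.75 + 0.03 × 0.15) = 1632 × 0.732 ≈ 1195. The formula needs about 49, which is the size of TP+FN.

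**The case against.** The best defence is that this is a labelling fault. Formula, inputs and result are printed together, so a careful reader can recover that W is a half-width, and the methodological sources cited for the formula may use the word width in that sense. Those sources are not at hand, so what was intended cannot be settled. This bears on the remedy: if a half-width was meant, rewording is enough. It does not rescue the text, which gives a reader no sign that 10% is anything but the full width.

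The second point is that 3% is the least favourable prevalence in the stated range, and the promised width is reached from about 12% upward. That is correct, and the 20-point figure should always be quoted with its 3% condition. But the article attaches its precision claim to 3%, and there the claim fails.

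Third, specificity is also part of the primary outcome and is estimated well. With 1632 × 0.97 ≈ 1583 culture-negatives, the half-width at 75% is 1.96 × √(0.1875/1583) = 2.1 points, a total of about 4.3. This limits the criticism to sensitivity. The formula was written for sensitivity, so the criticism of it stands.

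Finally, the TN+FN slip has no numerical effect, because the right-hand side of the formula is correct. That is true, but it is still an error in a published formula.

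**Conclusion.** The concern holds. At the plan's own inputs (sensitivity 85%, culture positivity 3%, 1632 evaluable ddPCR patients, two-sided 95% interval), the expected total width is 20 points, twice the stated 10. The sample-size arithmetic is sound. What is wrong is the precision statement and the numerator of the formula.

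The size of the discrepancy depends on positivity: the width falls to 11.0 points at 10% and 8.9 at 15%. It depends little on the interval method. It also grows somewhat if sensitivity is lower: at the 80% that the Discussion cites from an earlier study of 45 blood samples, the half-width with 49 culture-positives is 1.96 × √(0.16/49) = 11.2 points. That estimate is itself imprecise, so it serves only to illustrate.

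**What to change.** In the Sample size calculation section:

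1. State the target as a 95% CI half-width of 10 percentage points (total width 20) for sensitivity at 3% culture positivity, and define W as the half-width.
2. Replace (TN+FN)/P with (TP+FN)/P.
3. Add the expected total width across the 3% to 15% range, as in the second table above.

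This changes text only. Enrolment, allocation and analysis stay as they are; the cost is a less favourable precision statement. If the sponsor did intend a total width of 10 points, it should say so and acknowledge that the present size delivers it only from about 12% positivity.

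An optional gain would be to run ddPCR, after day 90, on stored day-0 samples from culture-positive controls. With 2176 × 0.03 ≈ 65 culture-positives overall, the half-width would fall from 10.0 to 8.7 points. This has clear limits: the samples may have been used for other tests, performance on stored blood would need justifying, and the results would inform sensitivity only and could not simply be pooled into the paired McNemar analysis. The correction does not depend on it.

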### Outcome measures

The primary outcome of this trial is the diagnostic efficacy of the ddPCR assay (the index test). The estimated sensitivity and specificity will be determined by comparing ddPCR assay results with the synchronous blood culture (the reference test) results from the prospective clinical specimens. Secondary outcomes between two arms consist of clinical outcomes and surrogate endpoints and fall into four categories: ① Clinical indicators: mortality rates at follow-up time points until day 90, the mean Sequential Organ Failure Assessment (SOFA) score at follow-up time points, the length of stay in the hospital or in the ICU, time to remission from shock (if there is septic shock), duration of mechanical ventilation or vasoactive drug application, rates of new requirement for renal replacement therapy;② Microbial and antibiotic usage indicators: time from enrollment to identification of a pathogen or the directed antimicrobial therapy, duration of major broad-spectrum antibiotics(glycopeptide, carbapenem) use, duration of antibiotic use;③ Quality of life indicator: the EQ-5D-5L score on day 90, which is a standardized measure of health-related quality of life developed by the EuroQol Group comprising five dimensions: mobility, self-care, usual activities, pain and discomfort, and anxiety and depression.④ Health economic indicators: total cost during hospital stay.

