## Background

Sepsis is life-threatening organ dysfunction caused by a dysregulated host response to infection [1]. It is considered a significant health concern worldwide for its high morbidity and mortality, which is between one in three and one in six [2]. As a medical emergency, early identification and management are crucial to better clinical outcomes. According to the 2021 Surviving Sepsis Campaign (SSC) guidelines, there is a strong recommendation for administering antimicrobials immediately, ideally within one hour for adults with possible septic shock or a high likelihood for sepsis [2]. The delayed initiation of effective antimicrobial therapy results in worsened outcomes [3], antibiotic misuse problems and a heavier health economics burden.

In clinical practice, physicians count on the information of the causative pathogens to start a precise antimicrobial therapy, highlighting the need for rapid and accurate pathogen identification tools. Currently, blood culture (BC) with antimicrobial susceptibility testing (AST) is the gold standard for diagnosing bloodstream infections (BSIs). However, this standard management is limited by a rather longer turnaround time (TAT). It takes around one to three days for the organisms, sometimes 28 days for the tuberculosis, to be cultured on the specific medium and additional one to two days to provide AST results [4, 5]. The sensitivity of the blood culture is relatively low and it can sometimes give false-positive results because of contamination [4, 6].

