### Statistical methods

Continuous general characteristics and laboratory test variants will be described by medians when they do not conform to the Kolmogorov–Smirnov test and by means when do. The Chi-square test will be used to evaluate independent binomial variables. All hypothesis tests are two-sided except for the primary outcome and a p value < 0.05 is considered of significance. For the primary outcome, the paired results of the ddPCR assay and BC will be analyzed using McNemar's test. Wilcoxon rank-sum test will be used to compare efficacy grades, Fisher's exact test to compare effective rates, and CMH (Cochran-Mantel–Haenszel) method to compare the efficacy grade and response rate after deducting the central effect. Multivariate analysis of multivariate mixed effects logistic regression can be used for outcome variables, and multivariate analysis of variance-adjusted Cox models can be used for time-event outcome variables. Apart from multivariate analysis, and propensity score methods may be used to control bias. In this trial, there will be an intention-to-treat (ITT) analysis as randomized analysis, including that of discontinuation and deviation. Also, sensitivity analysis will be used to ensure appropriate interpretation. Methods like multiple imputation will be used to handle missing data. Figures and statistical analyses will be conducted using the Prism 9.0 software (GraphPad Software, San Diego, CA, the USA), SPSS Version 20.0 (IBM Corp., Armonk, NY, USA), and R studio 4.0.3 software (R studio Software, Boston, MA, USA).

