The PROGRESS trial is a comparative effectiveness research (CER) for the purpose of evaluating an alternative health-care intervention, which, in this case, is the appliance of a rapid ddPCR diagnostic assay. It can also be classified as a practical RCT (pRCT), and the pragmatic approaches are taken in many aspects. Firstly, the inclusion criteria are designed to enroll any adult patient with suspected sepsis who is likely to be provided the intervention, including people who are immune compromised, with multiple morbidities, or over the age of eighty. Secondly, to set the situation as consistent as possible with the real-world condition, we do not interfere with other pathogen tests that clinicians may choose. Microbial examinations like mNGS are accessible to both the experiment group and the control group. Thirdly, except for day 90 follow-up on the phone, the follow-up will be completed during the patients’ hospital stay. Lastly there will be an intention-to-treat analysis using all available data. It not only maintains a relatively high internal authenticity through the randomized controlled trial design, but also takes into account generalizability and feasibility in ‘the real world’ when assessing the benefits of the ddPCR assay [28].

There are also several limitations about this trial. One limitation is that when calculating turnaround time, we assume the availability of the ddPCR assay is equal to that of standard blood culture, and it is not true. The ddPCR assay hasn’t been integrated into the usual clinical procedures. It is only available for twelve hours during the daytime on weekdays because of the limited number of trained staff to run the ddPCR test at this day. We believe next steps for such a novel mRDT will be making the process of handling samples and interpreting results easier to operate, as well as minimizing the need for technical expertise. And we will add the waiting time into the turnaround time in the final analysis when comparing with that of the blood culture. Also, the assay only includes the fifteen most common detected pathogens in BSIs. It cannot investigate unknown emerging pathogens, and the ddPCR panel’s ability to expand is to be studied. Moreover, since it is not a double-blind RCT, bias such as clinical decision-making preferences are inevitable. And as a comparative effectiveness research and a real-world study, statistical methods need to be taken to further control the confounding factors.

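### Mean SOFA at in-hospital time points that are not stated as common to both arms can make the arm that saves or discharges more patients look worse

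*Protocol article*

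**What the plan says.** The section on outcome measures lists, among the secondary outcomes compared between the two arms, "the mean Sequential Organ Failure Assessment (SOFA) score at follow-up time points". It also lists length of stay, "duration of mechanical ventilation or vasoactive drug application", durations of antibiotic use, and "Quality of life indicator: the EQ-5D-5L score on day 90".

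The Discussion says that "except for day 90 follow-up on the phone, the follow-up will be completed during" the hospital stay.

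The section on duration of follow-up gives one calendar, and it is for blood collection. In the ddPCR arm, patients positive on day 0 are sampled on day 3, day 7 and weekly thereafter until a clinical outcome. For the others, "The patients with negative results for the first time on day 0 will have blood collected every seven days", with extra tests from day 3 if the physician asks. "For the control group, blood samples will be collected on day 0, and stored in the laboratories of participating institutions", and no later day is given for that arm. The next paragraph adds the laboratory and bedside items needed for SOFA to the follow-up examinations, without naming days. Day-90 vital status and EQ-5D are obtained by telephone.

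The section on statistical methods states an intention-to-treat analysis, unspecified sensitivity analyses and Cox models for time-to-event outcomes. It adds: "Methods like multiple imputation will be used to handle missing data". It does not separate a score that was missed from one that cannot exist because the patient has died.

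**The concern.** A mean SOFA on a given day, taken from scores recorded in hospital, describes the patients who are alive and undischarged on that day. Faster pathogen identification is meant to change who dies and who goes home, so membership of that group may itself depend on the arm. The comparison is then no longer between the groups formed by randomisation. If one arm keeps very sick patients alive, they enter its mean with high scores. If it sends recovering patients home sooner, their low scores leave its mean. Either way the better arm can show the higher value.

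This matters because the primary outcome is a paired accuracy comparison within the ddPCR arm. The control arm and the randomisation serve only the secondary outcomes, and the Discussion relies on them to show whether ddPCR-guided treatment changes the clinical course. The Background describes sepsis as having "high morbidity and mortality, which is between one in three and one in six", so loss of scores through death may be substantial.

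**Working it through.** The plan gives no figure on this point to reproduce. Its sample size of 2292 rests on the precision of sensitivity alone. Every score, discharge rate and effect below is an assumption; only the mortality range of one in six to one in three, used in steps 4 and 5, comes from the protocol article.

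**1. Base case.** Per 100 control patients on a given day: 20 dead, 20 discharged, 30 in hospital at SOFA 1, 30 in hospital at SOFA 6.
Observed mean = (30×1 + 30×6)/60 = 210/60 = 3.5.

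**2. ddPCR discharges 10 more of the patients at SOFA 1; nothing else changes.**
Observed mean = (20×1 + 30×6)/50 = 200/50 = 4.0, which is 0.5 higher than control.

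**3. ddPCR instead saves 5 patients, who are in hospital at SOFA 9; nothing else changes.**
Observed mean = (30×1 + 30×6 + 5×9)/65 = 255/65 = 3.92, which is 0.42 higher than control.

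In neither case is any patient worse off. The condition is that saved patients score above the average of the other inpatients, or that the extra discharged patients score below it.

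**4. Other assumptions.**
- *Death.* Other survivors score 5; saved patients score 10 or 12. With mortality 33.3% v 28.3%, the ddPCR mean is (0.667×5 + 0.05×10)/0.717 = 5.35, or 5.49 with 12, a difference of +0.35 to +0.49. With 16.7% v 13.7%, it is (0.833×5 + 0.03×10)/0.863 = 5.17, or 5.24 with 12, a difference of +0.17 to +0.24.
- *Discharge.* Mortality m is equal in both arms, 20% of controls are discharged, and a further share e (5 or 10 points) is discharged under ddPCR. Those patients score 2 and the rest 6. The control mean is [2e + 6(h − e)]/h with h = 1 − m − 0.20; the ddPCR mean is 6. With m = 1/3 the control mean is 5.57 or 5.14 (difference +0.43 or +0.86). With m = 1/6 it is 5.68 or 5.37 (difference +0.32 or +0.63).

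**5. The other outcomes, where only death matters.**
- *Antibiotic days*, with 4 in patients who die and 12 in survivors. Mortality 25%: 0.25×4 + 0.75×12 = 10.0. Mortality 20%: 0.20×4 + 0.80×12 = 10.4. The mean rises by 0.4 days with no change in prescribing.
- *Length of stay*, with 5 days in patients who die, 25 in saved patients and 15 in the others: 11.67 v 12.67 days (mortality 33.3% v 28.3%), or 13.33 v 13.93 days (16.7% v 13.7%).
- *EQ-5D*, with 0.40 in saved patients and 0.75 in other survivors. Among survivors only, at 33.3% v 28.3%: (0.667×0.75 + 0.05×0.40)/0.717 = 0.726 v 0.750, a difference of −0.024. At 16.7% v 13.7% it is −0.012. With death scored 0, the values are 0.520 v 0.500 (+0.020) and 0.637 v 0.625 (+0.012), so the sign reverses.

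**6. Steps 2 and 3 with all patients ranked** (death worst, then higher SOFA, lower SOFA, live discharge best). The measure is the probability that a ddPCR patient does better than a control patient, counting ties as half; 0.5 means no difference.
- *Earlier discharge:* better = 0.3×0.8 + 0.2×0.5 + 0.3×0.2 = 0.40; ties = 0.04 + 0.09 + 0.06 + 0.06 = 0.25; result 0.40 + 0.125 = 0.525.
- *Saved patients:* better = 0.2×0.8 + 0.3×0.5 + 0.3×0.2 + 0.05×0.2 = 0.38; ties = 0.03 + 0.09 + 0.09 + 0.04 = 0.25; result 0.38 + 0.125 = 0.505.

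Both now favour ddPCR, the arm in which patients did better.

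**The case against.** The strongest reply is that this is a condensed article and that the handling of death in SOFA, durations and EQ-5D usually sits in an analysis plan, which is not shown. That stands for the detail. It does not cover the summary the article itself fixes: a mean, taken during the hospital stay, with generic imputation. Nor can an analysis plan recover scores on days when they were not collected.

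A reader might also infer several stronger things that the text does not support:

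- *That all these outcomes are compared only in inpatients.* No section says so, and intention-to-treat is stated. EQ-5D is collected by telephone, so discharged survivors contribute. Durations can be recorded for every patient. Earlier discharge shortens the stay and counts in an arm's favour there, so the discharge mechanism applies to SOFA alone.
- *That SOFA follows the arm-dependent calendar, leaving a day-3 mean without a control counterpart.* The calendar is written for blood collection, and the control sentence concerns a stored sample. The article names no day-3 mean, mentions a uniform case report form, and its flowchart is not shown. What stands is that no SOFA days common to both arms are stated.
- *That scores will be imputed for the dead.* The sentence on imputation is general. It neither says this nor excludes it.
- *That the sign will reverse.* It can, under the condition in step 3. The cited mortality describes sepsis. The trial enrols patients with two SIRS criteria and a blood culture, and their mortality may differ.

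Mortality to day 90 is itself a listed outcome, so a survival difference would be visible beside the SOFA result. That helps interpretation but does not repair the SOFA comparison.

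**Conclusion.** The point holds for SOFA. Followed as written, the protocol gives a mean that depends on being alive and undischarged, or one completed by imputation that has no meaning after death, at time points not stated as common to the arms. The comparison can disfavour the arm that saves or discharges more patients. Under the assumed values, the observed mean in that arm is 0.17 to 0.86 points higher with no patient worse off. The direction follows from the mechanism when its condition is met; the size rests wholly on the assumptions.

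For durations and day-90 EQ-5D the point is weaker and concerns death only: durations are cut short by it, and EQ-5D can come only from survivors. All affected outcomes are secondary. The accuracy outcome and the sample size do not change.

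**What to change.** - State the SOFA assessment days, the same for both arms and regardless of ddPCR result.
- Compare all randomised patients on those days by a rank-based or ordinal analysis, with death as the worst category and live discharge in a prespecified favourable one. Do not impute SOFA after death; keep multiple imputation for scores missed in living patients.
- Analyse durations as days alive and free of the item to a fixed day, or with death as a competing event.
- Include deaths in the EQ-5D index, for example as 0, and give survivor-only results as supportive.

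The cost is some wording and a common schedule on the case report form, mostly using routine laboratory and bedside data. The SOFA result becomes less simple to read than a difference in means. No extra patients are needed.

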### Setting

This multi-center trial is set in the infectious disease departments and ICUs of ten hospitals, which are distributed across five provinces in China: Huashan Hospital Affiliated to Fudan University, Central Hospital of Minhang District, Xinhua Hospital Affiliated to Shanghai Jiao Tong University School of Medicine, and Shanghai Sixth People’s Hospital Affiliated to Shanghai Jiao Tong University School of Medicine in Shanghai; Nanjing Hospital of Chinese Medicine Affiliated to Nanjing University of Chinese Medicine and Wuxi No. 5 People’s Hospital in Jiangsu Province; Ruian People’s Hospital and The First Affiliated Hospital of Wenzhou Medical University in Zhejiang Province; Xiangya Hospital Central South University in Hunan Province; The First Affiliated Hospital of Anhui Medical University in Anhui Province. The Huashan PROGRESS project team is the trial sponsor and is responsible for the design and supervision throughout this trial.

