### Study population

Adult patients who meet the inclusion criteria and none of the exclusion criteria will be eligible to participate in this trial (Table 1). They will be enrolled after providing the informed consent to their physician and the Huashan PROGRESS project team.

**Table 1 Tab1:** Inclusion criteria and exclusion criteria

Inclusion criteria: 1. 18 years old or older 2. Meet at least two of SIRS^a^ criteria: ➀ Temperature > 38 ℃ or < 36 ℃ ➁ Heart rate > 90 bpm ➂ Respiratory rate > 20 or PaCO_2_ < 32 mmHg ➃ WBC > 12,000/µL or < 4000/µL or > 10% bands 3. Hospitalized patients who have a diagnostic blood culture drawn on the same day as enrollment (day 0), which is the standard procedure for suspected sepsis 4. Written informed consent signed by the patient or their legal representative Exclusion criteria: 1. Refusal to participate in the study or failure to comply with treatment or follow-up 2. Known pregnancy or lactation 3. The researcher believes that there are any conditions (social or medical) that allow subjects to participate is unsafe. For example, severe anemia or high risk of bleeding, etc., which are not suitable for taking peripheral blood for testing 4. Participating in other clinical studies	

*SIRS*^a^ system inflammatory reaction syndrome

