### Blinding

There is no blinding in this trial. After randomization, the group information with corresponding procedure is open to the participants, their physicians and the project team. The Huashan PROGRESS project team will have access to the final trial dataset, and investigators from cooperative hospitals will have access to the data from their respective hospitals.

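### Hospital cost, hospital or ICU stay and shock remission are not tied to day 0, so pre-randomisation charges and days, and shock that begins after randomisation, can enter the arm comparison

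*Protocol article*

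**What the plan says.** All references are to the protocol article.

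- **Who is enrolled.** Table 1 under Study population requires "Hospitalized patients who have a diagnostic blood culture drawn on the same day as enrollment (day 0"). The criteria set no limit on days already spent in hospital. Under Setting, "This multi-center trial is set in the infectious disease departments and ICUs of ten hospitals", so some patients may already be in an ICU at enrolment. Entry needs two SIRS criteria and a blood culture; shock is not required.
- **Time zero.** Duration of follow-up fixes it: "On the same day as randomization, which is counted as day 0".
- **Stay and shock.** Outcome measures lists "the length of stay in the hospital or in the ICU, time to remission from shock (if there is septic shock"). No start is given for stay. Nothing says when shock must be present or from when remission is timed.
- **Cost.** The one health economic indicator is "total cost during hospital stay".
- **Neighbouring endpoints that are tied down.** The same list has "time from enrollment to identification of a pathogen or the directed antimicrobial therapy" and "rates of new requirement for renal replacement therapy". The first has a stated origin and the second is limited to new events.
- **Blinding.** "There is no blinding in this trial"; the section adds that the project team knows the allocation.

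**The concern.** There are two separate problems, and they differ in kind.

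**Cost and stay.** A patient in whom sepsis is suspected late in an admission brings charges and days that had accrued before any ddPCR result could exist. If they are counted, the comparison carries variation with no information about the intervention, and a real effect on cost or stay is harder to see. This matters because the Background faults earlier studies for not evaluating clinical impact or cost-effectiveness, and total cost is the only economic endpoint here.

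**Shock remission.** Since shock is not an entry criterion and the endpoint is not limited to shock at day 0, shock that begins later fits the wording. The trial's rationale is that faster directed therapy improves outcomes, so the intervention could change who develops shock. A comparison among patients who did would then not be protected by randomisation. If ddPCR-guided therapy prevented some milder late cases, the remaining ddPCR shock cases would be sicker on average, and that arm could look worse because it had benefited.

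**Working it through.** **The plan's own figure.** The section Sample size calculation gives sensitivity 0.85, W = 0.10, prevalence 0.03 and alpha 0.05:

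N1 = 1.96² × 0.85 × 0.15 / (0.10² × 0.03) = 1632.6 (stated 1632)

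1632 / 3 × 4 = 2176, and 2176 / 0.95 = 2290.5 (stated 2292, which is the next multiple of 4). The figure reproduces. It rests on sensitivity alone, so no power was planned for cost, stay or shock, and redefining them leaves the sample size unchanged.

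**Cost and stay: effect of counting time before day 0.** Write the whole-stay value as A + B, with A before and B after randomisation.

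1. Randomisation makes the mean of A equal in expectation in both arms, so the expected difference in means is the difference in B. There is no bias.
2. If A and B are independent and SD(A) = k × SD(B), then Var(A + B) = (1 + k²) × Var(B).
3. The documents give neither k nor the correlation of A with B. The values of k below are assumptions. A positive correlation would make the factor larger and a negative one smaller.
4. Take 1632 against 544 evaluable patients and a difference detectable with 80% power on B alone: (1.96 + 0.8416) × √(1/544 + 1/1632) = 0.139 SD.

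| k (assumed) | Variance factor 1 + k² | 2176 / factor | Power for that difference |
|---|---|---|---|
| 0 | 1.00 | 2176 | 80% |
| 0.25 | 1.06 | 2048 | 78% |
| 0.5 | 1.25 | 1741 | 71% |
| 1 | 2.00 | 1088 | 51% |
| 1.5 | 3.25 | 670 | 34% |

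The cost ranges from negligible to substantial, and nothing in the documents locates the trial within it. The factor applies to a difference in means; it does not carry over exactly to the Cox models that Statistical methods names for time-to-event outcomes.

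**Shock remission: effect of admitting later cases.** An illustrative simulation used inputs that are all assumptions: about 10% of patients in shock at day 0, about 8% developing it later, more severe patients at higher risk and slower to recover, and no effect of ddPCR on recovery time. In one arm, some later cases were prevented, all from the milder half.

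| Share of later cases prevented (assumed) | Ratio of mean recovery times, all shock cases |
|---|---|
| 0% | 1.00 |
| 10% | 1.02 |
| 20% | 1.04 |
| 30% | 1.06 |

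The true ratio is 1.00 throughout. The shift goes against the arm that prevented cases. In the subset with shock at day 0, which is fixed before the intervention can act, there is no shift.

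**The case against.** The strongest reply is that a journal article may leave clock origins and subset definitions to the full protocol, the SAP or the case report form, and that the trial has a clear day 0 from which these endpoints may well be counted. Much of that stands.

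- **Stay.** A reader might infer that the plan defines hospital and ICU stay as whole-admission totals. It does not. The whole admission is the ordinary meaning of the term, but counting from day 0 is compatible with the text.
- **Ventilation, vasoactive drugs and antibiotics.** A reader might extend the criticism to these durations. They are listed without an origin, and nothing states them as whole-stay totals.
- **Shock.** A reader might infer that everyone who ever has septic shock is deliberately included. The wording does not exclude later shock, but shock at enrolment is an equally natural reading.
- **Size.** An effective sample of 1741 or 1088 might be read as this trial's expected loss. Both come from an assumed k, and no power was planned for these endpoints. Likewise, the 2% to 6% shift in recovery time rests on assumed rates.
- **Whole-stay cost** can be defended as relevant to payers in a pragmatic trial, and counting it does not bias the comparison.

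Two things survive. The cost wording is a positive definition which, followed as written, takes in charges before day 0. The shock condition, applied as written, admits cases that begin after randomisation. The same list gives an origin to one endpoint and a new-event limit to another, so these two are inconsistent with their neighbours rather than merely abbreviated.

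**Conclusion.** The point holds for cost and for the shock subset. For hospital and ICU stay it holds only as an undefined origin.

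For cost and stay the consequence is lost precision, not bias in the difference in means: a variance factor of 1 + k² under independence, with k unknown. For shock remission the consequence is a possible bias, because the subset may depend on the arm. Its existence requires that the intervention changes who develops shock after day 0, and its size cannot be obtained from the documents. The shock part therefore matters more in kind, although its illustrated size is small.

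All the endpoints concerned are secondary. The primary diagnostic outcome and the sample size are untouched. The definitions should be corrected before the arms are compared, because the trial is open label and an origin left undefined could be chosen with the data in view.

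**What to change.** In Outcome measures, and in the SAP if it does not already say so:

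1. Compare total cost and hospital and ICU stay from day 0 to discharge. Keep whole-admission totals as descriptive figures, which preserves the payer's view.
2. Restrict time to shock remission to patients in septic shock at day 0, timed from day 0.
3. Report new septic shock after day 0 as a separate outcome in all randomised patients, so that any preventive effect is counted directly.
4. Give the ventilation, vasoactive-drug and antibiotic durations the same day-0 origin, as a clarification.

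The cost is a change of wording plus dividing each hospital bill at day 0. Admission, randomisation and discharge dates and dated charges should be in the hospital record. The shock-remission analysis will have fewer patients. Eligibility, treatment, sample size and the primary analysis do not change.
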